# Effect of availability of HIV self-testing on HIV testing frequency among men who have sex with men attending university in China (UniTest): protocol of a stepped-wedge randomized controlled trial

**DOI:** 10.1186/s12879-020-4807-4

**Published:** 2020-02-18

**Keywords:** HIV self-testing, Young men who have sex with men, Student, Stepped-wedge design

## Abstract

**Background:**

HIV testing plays a central role in the combat against HIV. We aimed to determine if the availability of HIV self-testing (HIVST) would increase the frequency of testing among men who have sex with men (MSM) attending university in China.

**Methods:**

A stepped wedge randomized controlled trial will be conducted in 4 provinces in China: Chongqing, Guangdong, Shandong, and Tianjin. Eligibility assessment will include (1) male, aged 16 years or older, (2) university student (technical diploma and undergraduate students), (3) MSM (sexual behaviors including mutual masturbation, oral sex, and anal sex), (4) HIV negative, and (5) willing to provide informed consent.

Participants will be randomly allocated to HIV self-testing intervention with free HIVST kits in every 30 days according to the intervention waiting lists with a computer-generated randomized sequence. All participants will complete a self-administrated online questionnaire onsite at baseline and 12-month follow-up and complete an online questionnaire at 4- and 8-month.

The primary outcome is the effect of HIVST on HIV testing frequency. Secondary outcomes include the change in sexual behaviors and HIV incidence.

**Discussion:**

No previous study had measured the effect of social media based HIVST intervention on the change in HIV testing behaviors, sexual behaviors and incident HIV infection among MSM attending university in China. Findings from this study will provide evidence for further interventional practice promotions and prevention strategies scale-up, including HIV testing, pre-exposure prophylaxis (PrEP) or post-exposure prophylaxis (PEP), and sexual partner serosorting.

**Trial registration:**

Chinese Clinical Trial Registry: ChiCTR1900020645. Registered 11 January 2019.

## Background

University students in China are facing increasing risk of human immunodeficiency virus (HIV) transmission [1]. According to the National Center for AIDS/STD Control and Prevention (NCAIDS), from 2011 to 2015, the number of university students infected with HIV increased by 35% annually [2]. The five years (2013–2017) surveillance reported 12,037 newly diagnosed student HIV cases, 97.7% were male, and 82.2% were men who have sex with men (MSM) [3]. MSM attending university refers to male university students who have oral or anal sex with other men, regardless of their sexual orientation or sexual identity. Systematic reviews found that the HIV prevalence among this population was 3.8% [4] to 4.4% [5]. Studies found high (65.2%) unprotected anal intercourse (UAI) in the past 6 months and low (57.5%) condom use in last anal intercourse among them [4].

Since the Joint United Nations Program on HIV/AIDS (UNAIDS) set up the ‘90–90-90’ goal to end the HIV epidemic by 2030, HIV testing has been placed in the forefront to ensure early detection and treatment of HIV case [6]. China has adopted an active approach of HIV testing in high-risk groups such as injecting drug users (IDUs), sex workers and MSM since 2004 [7]. In 2014, 1881 HIV sentinel surveillance sites completed the HIV testing of 750, 000 people in China [8]. Although HIV testing coverage has been steadily increasing, only half of MSM had ever tested for HIV [9, 10]. Stigma, discrimination, and lack of privacy are barriers for MSM to access HIV testing [11, 12]. HIV self-testing (HIVST) is a process that a person takes and interprets a test, which is recommended by the World Health Organization (WHO) as an acceptable, private, and convenient approach to HIV testing [13, 14]. Currently only one urine-based HIV self-test was officially approved by health authorities in China [15]. Some studies reported that between 29% and 40% of participants had conducted HIV self-testing among Chinese MSM [16, 17]. An internet-based HIVST study suggested HIVST can promote active testing, eliminate the concern of privacy disclosure, and improve the accessibility and pertinence of HIV testing among MSM in China [18]. According to *The China Action Plan for the Thirteenth Five-Year Plan for Combating and Prevention of AIDS* which was issued by the State Council of China, self-testing should be applied to scale up HIV testing [19].

MSM attending university are a unique subgroup of the MSM community. Understanding the key factors of HIV transmission among this population is crucial to providing sufficient support and services. HIV prevention among MSM attending university will largely depend on interventions that can reduce unprotected sex and increase the frequency of HIV testing. In recent years, with the increasing promotion of HIV testing within the MSM community, more MSM started to access HIV and other sexually transmitted infections (STIs) testing services, supposedly increasing the frequency of testing among students. Despite these efforts, large numbers of students living with HIV are unaware of their status, increasing chances of immune deterioration and secondary transmission [20–23]. Compared to general MSM, there are additional barriers to HIV testing among students, including low-risk perception, poor knowledge and understanding, fear of positive diagnosis, concern of disclosure of sexuality, and limited access and testing resources [24]. HIVST may be a potential approach to increase access to HIV testing for students who avoid in-person HIV testing sites due to perceived challenges to confidentiality [25, 26].

HIV-related research among MSM attending university in China is limited by low representativeness (i.e., samples were a small fraction of general MSM). Within China, prevention efforts for MSM attending university are significantly weaker in evidence base than those for other high-risk groups. The limited data generated by cross-sectional studies to date cannot provide accurate estimates of HIV infection and characterize the factors driving transmission among MSM attending university in China, which further inhibits the development of effective interventions for this population. Prospective surveys among this population will be more helpful in understanding the risks for HIV infection and the effectiveness of interventions among MSM attending university. Effective intervention approach (i.e., availability of HIV self-testing) which can facilitate HIV diagnosis and prevent secondary transmissions also needed to be developed and evaluated using rigorous methodologies.

## Methods/design

### Study aims

The University Student HIV Test Intervention Study (the UniTest Study) aims to conduct a randomized controlled trial (RCT) with a stepped-wedge design to evaluate the effect of HIVST intervention on HIV testing frequency, HIV related high-risk behaviors and HIV incidence among MSM students attending university in China.

### Study design

We will use a stepped wedge trial (SWT) design to implement HIV self-testing intervention. Participants will randomly receive HIVST intervention at different time points. Unlike the traditional parallel designed trials, in an SWT participants are randomly allocated to the order of implementation, such that all participants eventually receive the intervention [27, 28]. The SWT design is recommended for trials that the intervention will do better than harm [29], such as HIVST intervention. Compared to parallel design, the SWT design maximizes statistic power and needs fewer clusters [30]. In our study, we will gradually implement HIVST intervention every 30 days according to the intervention waiting lists with a computer-generated randomized sequence.

### Study population

#### Inclusion criteria

Individuals are eligible if they meet the following criteria: 1) Male, aged 16 years or older. 2) University student (technical diploma and undergraduate students). 3) MSM (sexual behaviors including mutual masturbation, oral sex, and anal sex). 4) HIV negative. 5) Willing to provide informed consent.

### Sample size

The sample size is calculated based on the HIV testing rate of MSM. A systematic review showed that just over 40% of MSM attending university in China had HIV testing in lifetime [9]. The HIV testing rate of the control group is estimated to be 40.0% (*p*_0_ = 0.40); Anticipated HIV testing rate of the intervention group will increase to 60% (*p*_1_ = 0.60), a total of six clusters, six total intervention time periods, a coefficient of variation of 0.4, two-sided *α* = 0.05, and 90% power. The annual loss to follow-up rate of the general MSM is 30.0%. The sample size is 408 (68 for each cluster). To further improve the power for sub-analysis, we increased the sample size by 10% to 448 (112 for each region) (see Additional file 1) [27].

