### Outcome measures

The primary outcome is the change in frequency of HIV testing comparing before and after intervention. Secondary outcomes include the change in sexual behaviors comparing before and after intervention, and HIV incidence comparing before and after intervention (Table 3).

**Table 3 Tab3:** Key indicators of the UniTest Study

Indicators		Definition
HIV testing Behavior	HIV testing in the control group	The frequency of HIV testing before receiving the intervention
	HIV testing in the intervention group	The frequency of HIV testing after receiving the intervention
	HIV testing reminders	The frequency of sending HIV testing reminders during the study period
	HIV self-testing kit application	The frequency of self-testing kits applications during the study period
	HIV self-testing result feedback	The frequency of self-test results feedback during the study period
Time indicator	Control time	The time interval of the participants to wait for receiving the intervention
	Intervention time	The time interval of the participants from receiving the intervention to the endpoint
HIV testing result	HIV infections	HIV infections detected during the study period
	HIV infections in the control group	HIV-positive individuals tested before intervention
	HIV infections in the intervention group	HIV-positive individuals tested after intervention

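### The stated 90% power is calculated for a lifetime testing proportion in six clusters, not for the planned comparison of testing frequency under individual randomisation

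*Protocol article*

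**What the plan says.** All inputs are in the Sample size section of the protocol article.

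- **Control value.** The source is a review finding that "just over 40% of MSM attending university in China had HIV testing in lifetime". The section then says: "The HIV testing rate of the control group is estimated to be 40.0" per cent. No time window is attached.
- **Intervention value.** "Anticipated HIV testing rate of the intervention group will increase to 60" per cent.
- **Design.** "a total of six clusters, six total intervention time periods, a coefficient of variation of 0.4", with "two-sided *α* = 0.05, and 90% power".
- **Loss.** "The annual loss to follow-up rate of the general MSM is 30.0" per cent.
- **Result.** 408 men, 68 per cluster, raised by 10% to 448, set out as 112 in each of four regions. Additional file 1 is cited for the calculation.

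Other sections describe the trial itself.

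- **Unit.** Study design: "Participants will randomly receive HIVST intervention at different time points". It and the abstract put the steps 30 days apart, following randomised waiting lists. No site, school or region is randomised.
- **Entry test.** Under Enrollment procedure and HIV testing, every man has a rapid test before joining, and only men who test negative are included.
- **Outcome.** Outcome measures: "The primary outcome is the change in frequency of HIV testing comparing before and after intervention". Table 3 counts tests before and after receiving the intervention and records each man's own control time and intervention time.

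**The concern.** A power statement is useful only if it refers to the quantity and design that will be analysed. This one differs from the trial in two ways.

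The first is the outcome. The 40% is the share of men who have ever been tested. Everyone enrolled has been tested at least once by the time he joins, so that measure is 100% from the first day and cannot be the outcome in this cohort. The named outcome is a frequency, and the section gives no control frequency, rate ratio or within-person variance for it.

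The second is the unit. A between-cluster CV describes natural groups whose underlying rates differ. Waves formed by randomising individuals differ only by chance. The correlation that does arise, repeated counts from the same man, does not appear among the stated inputs.

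At stake is how the result is read. A null finding would be judged against a 90% power that was never calculated for the primary comparison.

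**Working it through.** **1. The plan's own figure.** Inputs from the Sample size section: p0 = 0.40, p1 = 0.60, six clusters, CV 0.4, two-sided 5%, 90% power. Assumed: one cluster crosses at each of six steps after a baseline period (T = 7), τ = CV × p0 = 0.16, and variance at the mean proportion, s² = 0.25/N for N people per cluster-period. For this layout the standard (Hussey–Hughes) variance reduces to

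Var = 6·s²·(s² + 7τ²) / (35·s² + 140·τ²).

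- N = 18: Var = 0.00395, SE = 0.0629, 0.20/0.0629 = 3.18, power 89%.
- N = 19: Var = 0.00375, SE = 0.0613, 0.20/0.0613 = 3.26, power 90%. With the variance taken at p0, N = 18 is enough.
- N = 68 in every period: Var = 0.00109, SE = 0.0330, ratio 6.07, power above 99.9%. After 30% loss (47.6) it is still 99.9%.
- 68 people split over seven periods (9.7 each): power about 66%.

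No reading gives 68 per cluster at 90%. One route that does reach 408 is a parallel two-proportion test with continuity correction: 139.1, so 140 per arm and 280 in all; 280/6 rounds up to 47; 47/0.7 rounds up to 68; 6 × 68 = 408. That formula uses neither the CV nor the periods. Whether it was the route taken cannot be known from the article. The last step is consistent: 408 × 1.1 = 448.8, stated as 448.

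**2. The CV.** With τ = 0, Var = 6s²/35, and 12 per cluster-period give 92%. The CV of 0.4 therefore raises the requirement from 12 to 19.

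**3. Power if the proportions belong to a window.** No window is given, so three are assumed. With a constant hazard over L days, q0 = 1 − 0.6^(30/L) and q1 = 1 − 0.4^(30/L). Retained: 448 × 0.7 = 314, or 52 per wave. The variance formula is as in step 1, with s² = q̄(1 − q̄)/52, where q̄ is the mean of q0 and q1, and τ = CV × q0.

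| Assumed window | q0 | q1 | SE (CV 0.4; CV 0) | Power (CV 0.4; CV 0) |
|---|---|---|---|---|
| 365 days | 0.041 | 0.073 | 0.0156; 0.0133 | 52%; 66% |
| 180 days | 0.082 | 0.142 | 0.0223; 0.0181 | 77%; 91% |
| 120 days | 0.120 | 0.205 | 0.0266; 0.0212 | 89%; 98% |

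**4. The rate scale.** Assumed: 314 completers in six equal waves, seven 30-day periods, Poisson counts and a log-linear model with period effects. Information is computed under the alternative, so expected counts are 314/6 × rate × 30/365, multiplied by the rate ratio once a wave has crossed. The detectable ratio solves log(RR) = (1.96 + 1.28) × SE.

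| Control rate (tests per person-year) | Detectable RR at 90% power |
|---|---|
| 0.5 | 2.17 |
| 1 | 1.77 |
| 2 | 1.51 |
| 3 | 1.41 |

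An overdispersion factor of 2 halves the information, which is the same as halving the control rate. The entry for 1 test per year then becomes 2.17, and the entry for 2 becomes 1.77.

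**The case against.** Several points against the concern have force.

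- **The contrast is not impossible.** A reader might infer that 40% against 60% cannot occur in a cohort where everyone is tested at entry. That holds only for lifetime ever-tested as the endpoint, which no section proposes. A screening test does not stop 40% and 60% being tested in some later window. The fair criticism is that the window is missing and the planning value comes from a different measure.
- **The clusters may be the waves.** Six clusters with six intervention periods plausibly means six randomised waiting-list waves. The CV is then misplaced, but step 2 shows that it makes the calculation more cautious. A reader might infer that it inflates the power; it does not.
- **The total need not divide by six.** The increase to 448 is explained as support for sub-analyses and is laid out by region, so this is no evidence of error.
- **The loss of power can be exaggerated.** Applying a ratio of 1.5 to the 30-day control probability would give 28–37% for an annual window. That shrinks the planned effect: converting the protocol's own 60% as well gives a 30-day ratio of about 1.7 to 1.8 and the higher values in step 3.
- **Additional file 1 is not shown.** It may give a window, a formula or a within-person correlation, so it cannot be said that these were ignored. It could not, however, turn a lifetime proportion into a frequency or individual randomisation into cluster randomisation.

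The mismatch of outcome and unit stands, as does the failure of the stated inputs to give 68 per cluster.

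**Conclusion.** The concern holds in a limited form and should be fixed. The 90% power is attached to a proportion without a window, taken from a lifetime measure, and to a clustered design, while the primary comparison is testing frequency under individual randomisation. It also does not follow from its own inputs under a standard stepped-wedge calculation.

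A reader might go further and infer that the trial is underpowered. The documents do not support that. With no cluster variation, which is what individual randomisation implies, two of the three assumed windows keep power at or above 90% (91% and 98%) and the annual one gives 66%. On the rate scale, a ratio of 1.5, the same as 60/40, needs a control rate of about 2 tests per person-year for 90% power, and more with overdispersion.

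These figures rest on assumed windows and rates, a constant hazard, seven 30-day periods, 30% loss and tests that can be dated to a period. They do not model correlation within a man beyond the overdispersion factor. They show how far the power depends on what the section leaves open; they are not estimates of the trial's actual power.

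**What to change.** Keep n = 448 and withdraw the 90% statement. In its place, report the rate ratio for tests per person-time that is detectable with 448 men. Base it on individual randomisation to six waves with period effects, an allowance for within-person correlation or overdispersion, and 30% loss. Show it over a range of control rates, informed by the HIV testing behaviors module already in the baseline questionnaire (Table 2). Describe the six groups as randomised waves and drop the between-cluster CV.

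The cost is rewriting one paragraph and a short calculation; enrolment does not change. The downside is that the restated power may look less favourable than 90%.

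### The 408 men at 90% power do not follow from the printed stepped-wedge inputs under the basic Hussey-Hughes model; 408 matches a two-proportion calculation that uses neither the coefficient of variation nor the periods

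*Protocol article*

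**What the plan says.** The whole calculation is in the Sample size section of the protocol article. It sets the control rate ("The HIV testing rate of the control group is estimated to be 40.0" per cent) and the target ("Anticipated HIV testing rate of the intervention group will increase to 60" per cent), then lists "a total of six clusters, six total intervention time periods, a coefficient of variation of 0.4", two-sided alpha 0.05 and 90% power. It adds "The annual loss to follow-up rate of the general MSM is 30.0" per cent and concludes "The sample size is 408 (68 for each cluster". A further 10% for sub-analyses takes the target to 448, or 112 in each of four regions.

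The section cites Additional file 1 and a reference that the Study design section also cites for the stepped-wedge design. It names no formula. It does not say whether 68 is a count per cluster-period or a count of men per cluster, or whether 408 already includes the 30% loss. Under Control group and in Table 3 (Outcome measures), each man contributes waiting time as a control and then time after the intervention, so the same men are followed across periods.

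**The concern.** Inputs and result are presented as one calculation, and a reader will assume that the second follows from the first. The basic stepped-wedge model does not connect them. The 90% is the only power figure in the article, and the 448 target is 408 plus 10%. If 408 came from a formula that never used the coefficient of variation or the periods, the paragraph gives the wrong basis for its number. A reader then cannot tell what difference the design is able to detect, and so what a null result would exclude.

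The check takes the inputs at face value. Whether they suit the trial is a separate question.

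**Working it through.** **Inputs (Sample size section).** p0 = 0.40, p1 = 0.60, difference 0.20; I = 6 clusters; six intervention periods; coefficient of variation 0.4; two-sided alpha 0.05 (z = 1.96); power 90%; loss 30%.

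**Assumptions where the text is silent.** T = 7 (six steps after an all-control period) or T = 6 (no all-control period, no all-intervention period, or five steps with one doubled). Between-cluster SD tau = 0.4 × 0.40 = 0.16; 0.20 and 0.24 were also tried. Variance sigma² = 0.24 or 0.25.

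**Stepped-wedge formula.** With n men per cluster-period and s = sigma²/n,

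Var = I·s·(s + T·tau²) / [(I·U − W)·s + (U² + I·T·U − T·W − I·V)·tau²], and power = Φ(0.20/√Var − 1.96).

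Here U is the number of treated cells, W the sum of squared column totals and V the sum of squared row totals. For I = 6 and T = 7: U = 21, W = 91, V = 91. Then I·U − W = 126 − 91 = 35, and U² + I·T·U − T·W − I·V = 441 + 882 − 637 − 546 = 140. So Var = 6s(s + 7·tau²)/(35s + 140·tau²).

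**Results for T = 7, tau = 0.16 (tau² = 0.0256), sigma² = 0.25:**
- n = 68: s = 0.003676; Var = 0.004034/3.7127 = 0.001087; SE = 0.0330; 0.20/SE = 6.07; power over 99.9%.
- n = 68 × 0.7 = 47.6: SE = 0.0393; ratio 5.09; power 99.9%.
- n = 19: s = 0.01316; Var = 0.01519/4.0445 = 0.003755; SE = 0.0613; ratio 3.26; power 90.4%.
- n = 68/7 = 9.7 (different men in each period): SE = 0.0840; ratio 2.38; power 66.3%.

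**Across all the layouts, tau and sigma² above** (closed form and direct generalised least squares agree):

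| Reading | Power |
|---|---|
| 68 per cluster-period | over 99.9% |
| 68 per cluster-period, after 30% loss | 99.6% or more |
| 68 different men spread over the periods | about 63–70% |

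For 90% power the model needs 18 to 24 men per cluster-period. No row gives 90%.

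**A route that does give 408.** Two proportions, individually randomised:
- Uncorrected: n0 = [1.96·√(2 × 0.5 × 0.5) + 1.2816·√(0.24 + 0.24)]²/0.20² = 129.3 per arm.
- Continuity-corrected: (n0/4)·[1 + √(1 + 4/(n0 × 0.20))]² = 139.1, rounded up to 140 per arm, so 280 in total.
- 280/6 = 46.7, rounded up to 47 per cluster; 47/0.7 = 67.1, rounded up to 68; 68 × 6 = 408.

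This reproduces both the 68 and the 408. It uses the two rates, alpha, power, loss and the six clusters as a divisor, but neither the coefficient of variation nor the number of periods. Without the continuity correction the same chain gives 130 per arm, 44, then 63 per cluster, 378 in total.

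**Sensitivity to an unprinted input.** Let the cluster effect correlate at r between periods, so that the covariance of the cluster-period means is tau²[r·J + (1 − r)·Identity] plus sigma²/n on the diagonal (J is the matrix of ones). With n = 68, T = 7, tau = 0.16 and sigma² = 0.24, power is 98.0% at r = 0.8, 94.5% at r = 0.7 and 90.0% at r = 0.6. With n = 47.6, r = 0.7 gives 91.7% (T = 7) or 89.0% (T = 6).

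**The case against.** The strongest reply is that the article never says it used the basic model. It points to Additional file 1, which is not shown and may hold the derivation; an article may leave the formula there, so its absence is not a fault. The basic model also holds each cluster's effect constant over time. Relaxing that one unprinted assumption to an autocorrelation near 0.6 gives 90% at 68 per period with every printed input kept. This stands, and it limits the claim to the basic model: the figures cannot be called impossible to reconcile.

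It is also fair that 408 may already contain the loss. On the two-proportion route it does, and deducting 30% from 68 again would then be the wrong comparison. The conclusion does not depend on that deduction, because the basic model gives far more than 90% with or without it.

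Three stronger readings are tempting and are not supported:
- **That the trial is underpowered.** The 63–70% arises only if 68 different men are spread over the periods. The Control group and Outcome measures sections describe the same men moving from control to intervention time.
- **That the trial recruits far more men than it needs, or can detect a much smaller difference than 20 points.** The basic model counts each man's repeated readings as independent. The Questionnaire survey section schedules questionnaires only at baseline, 4, 8 and 12 months, and the primary outcome is testing frequency. These would be outputs of a model, not established properties of the trial.
- **That 408 is known to come from the two-proportion formula.** The match is exact, but the origin remains an inference.

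**Conclusion.** The point holds in limited form. Under the basic Hussey-Hughes model, the printed inputs do not lead to 408 men at 90% power: about 18 to 24 men per cluster-period would suffice, against 68 printed, and 68 gives over 99.9% (99.6% or more after loss) when the same men are followed. The one route found that returns 68 per cluster and 408 exactly leaves out two of the inputs given as the basis.

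This rests on a constant cluster effect, a normal-approximation test, repeated readings treated as independent, and tau equal to the coefficient of variation times a rate between 0.40 and 0.60. Additional file 1 could supply an input that closes the gap. In that case the Sample size section would still need that input stated, because the printed list does not lead to the printed result under the basic model. The fault lies in the justification of the sample size; it is not evidence that the enrolment target is too small.

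**What to change.** Keep the 448 enrolment target. Recompute from one named stepped-wedge model that uses the printed coefficient of variation and periods and allows for repeated measures on the same men. State any assumed autocorrelation and show results over a range of values. Say whether 68 counts men per cluster or per cluster-period, and where the 30% loss enters. Then replace the claim of 408 at 90% power with the power, or the difference detectable with 90% power, that 448 men with 30% loss give (448 × 0.7 = 313.6 retained, about 52 per cluster).

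If 408 did come from the two-proportion formula, say so and remove the coefficient of variation and the periods as its stated basis.

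The cost is a rerun of the calculation and a correction to a published justification. Enrolment and procedures do not change.
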